## Role of individualism and collectivism

Adding another layer of complexity, socio-cultural norms, such as individualism and collectivism, heavily influences how people conduct their lives and describes the degree of social cohesion in a society and an individual’s willingness to prioritize common goals over personal goals
^
39,
40
^. In India, collectivist and individualist values coexist and are also reflected in people's behavior
^
41
^. For example, some young Indians may move to urban centers for work and have an individualistic lifestyle there but send a large portion of their income to their families in rural areas demonstrating collectivism
^
41
^. Many studies have characterized India as a more collectivist-leaning society highly valuing an emotionally close, well-defined hierarchical family relationship, which leads to a strong sense of familial self rather than individualized self
^
39,
42–
44
^. In Sinha
*et al*.’s 2002 study on collectivist-individualist intentions and behavior, more than 60% of Indian participants faced with decisions involving their immediate family responded with collectivist behaviors supported by collectivist intentions
^
45
^. However, when participants faced decisions involving their larger community only 38% responded with purely collectivist behaviors and intentions
^
45
^. Thus, the familial social group evokes the strongest collectivist response among Indians, while more distal social groups are less likely to evoke a purely collectivist response and are more likely to elicit a mixture of collectivist and individualist intentions and behaviors.

Since vaccines protect both the individual and the larger community, both individualism and collectivistic attitudes may be relevant in understanding the effectiveness of vaccine communication. Collectivist intentions can decrease vaccine hesitancy and increase peoples’ willingness to get vaccinated. The importance of the group in collectivist societies leads to more consideration of others in decisions, including whether to be vaccinated
^
46
^. One reason for this is that collectivistic intentions are positively correlated with empathy and in a more empathetic society people are more likely to adopt key health precautions such as handwashing and vaccination in response to an increased perception of an infectious disease
^
47,
48
^. Emphasizing community benefits such as herd immunity in public health communication can increase COVID-19 vaccination in more individualistic cultures where people tend to focus on the benefits to the individual more than the group
^
46
^. Using data from the COVID-19 Beliefs, Behaviors, and Norms Survey, researchers compared vaccine uptake across 50 countries and found that vaccine intentions were higher in countries with more collectivist cultures and that individuals who endorsed collectivistic values were more likely to accept a COVID-19 vaccine
^
49
^. The extent to which this approach also applies to vaccination in India is unknown and is the subject of inquiry in this project. 

## Role of protagonist gender

Finally, from a practical perspective, vaccine promotion campaigns also need to make decisions about the kinds of sources they will feature. It is not uncommon to promote vaccination messages through the use of medical spokespersons, public health officials, or credible public health agencies like the Centers for Disease Control and Prevention and WHO
^
50,
51
^. The source of vaccine information has been strongly linked with trust in that information
^
52
^. Indeed, decades of communication research have found that information communicated by credible spokespersons are more persuasive for behavior change
^
53
^. Health communication research tends to focus on source credibility stemming from a spokesperson’s perceived competence and character, but sociodemographic factors – including a source’s race/ethnicity, gender, and social status -- can also have a significant impact on credibility
^
54,
55
^. Further, it is likely that concordance or homophily between a message’s source and audience can increase receptivity to health messages
^
56,
57
^. These effects vary by population, health topic, medium, and context.

With the COVID-19 pandemic, a new wave of research focuses on the impact of different spokespersons promoting vaccines – particularly to vaccine-hesitant communities
^
58
^. Much of this research is focused on US-based and European audiences, with fewer studies exploring messaging effects in low- and middle-income countries
^
51,
59
^. While concordance between spokesperson and audience is likely important for message tailoring, the culturally specific nature of gender roles and health messaging norms means that each context is likely unique.

India is a patriarchally-oriented society, but health decisions often fall to women
^
60
^. Women are also more likely to hold community health worker roles (including the all-women ASHA program) that are focused on promoting vaccines
^
61
^. While these factors may increase the source credibility of a female vaccine advocate, past research has shown that gendered norms may prevent women in Odisha from being seen as autonomous decisionmakers
^
62
^. The context of COVID-19 vaccine decisions may be unique. A qualitative study from Nair
*et al*. found that in Kerala India, men were more likely to be online and therefore more likely to consume COVID-19 vaccine-related messaging
^
63
^. While younger generations are challenging existing gender norms, for this audience, it isn’t known if a young male or a young female protagonist would be viewed as a more credible advocate for COVID-19 vaccination – or if gender is even relevant in this context. 

## Methods

### Institutional review board statement

The study was conducted in accordance with the Declaration of Helsinki and approved by the Institutional Review Board at The Johns Hopkins University (IRB00018543), 1/23/2022 and Sigma IRB (10075/IRB/21-22) in India on 12/20/2021.

### Study setting

This research was conducted in the eastern Indian state of Odisha, with a population of about 46 million people
^
64
^. In 2011, 83.3% of the state lived in rural areas, and 16.7% of the population lived in urban areas
^
65
^. Additionally, 40% of the state’s population belong to Scheduled Tribes (22.85%) or Scheduled Castes (17.13%)
^
65
^. Odisha is also a state with relatively high levels of childhood immunization. Between 2019 and 2021, 91% of children between 12–23 months received all basic vaccinations against tuberculosis, diphtheria, pertussis, tetanus, polio, and measles and 98% of children between 12–23 months were at least partially vaccinated against the six major childhood illnesses
^
64
^. 

There have been 1 million confirmed cases and 8,400 deaths reported since the start of the COVID-19 pandemic in Odisha
^
66
^. Vaccine distribution in the country is decentralized, with each Indian state responsible for local administration and vaccination rates vary widely by state
^
67
^. As of February 2022, 95% of individuals over the age of 18 years had received the first dose, 92% were eligible for a second dose, and 80.3% of all eligible individuals had received both doses, making vaccination rates in Odisha higher than the national average (Express News Service, 2022). 

### Research team

The research was conducted through a partnership between The Bloomberg School of Public Health, The Johns Hopkins University in the United States and D-COR Consulting in Odisha, India.

### Study design

An online experiment was conducted through a 2 (appeal: individualistic or collectivistic) x 2 (tone: humor or non-humor) x 2 (protagonist gender: male or female) between-subjects design. Participants were recruited through a link posted on the Swasthya Plus Network (SPN) Odia website, and was shared by SPN on their public Odia WhatsApp channels. In order to be eligible for the study, participants needed to be between the ages of 18–35, and speak Odia. We did not check for language ability as the recruitment pages, channel, survey, and videos were all in Odia. Odia-speaking participants (N = 2,700) between the ages of 18–35 years were randomly assigned to watch one of the eight study videos, providing their vaccination attitudes, beliefs, and intentions both before and after viewing the videos. We tested for main effects of appeal, tone, and protagonist gender (as well as the underlying two-way and three-way interactions). During script development, we also sought the feedback from a community advisory board for cultural appropriateness. Videos were shot in December 2021 and the experiment itself was launched in January 2022.

### Video scriptwriting

Many vaccination messages put out by the Indian government use a public service announcement structure in which people are urged to get vaccinated in order to ward off the disease and derive positive benefits, with a primary messaging strategy built around providing accurate vaccine information
^
68
^. In this project, we adopted a different approach so that our videos would stand out from the din of government-produced announcements. Borrowing ideas from entertainment education
^
69
^, we chose to depict a common social event (e.g., a child’s birthday) in which vaccination issues would be brought up in an incidental manner, not as the primary thrust of the communication.

The creative team identified various real-world mixed-gender, mixed-age settings that would fit these criteria. Finally, a private social occasion of the birthday of a young family member was selected to be the setting for the video. Within this broad setting, we manipulated appeal, approach, and gender to create eight videos that were identical, except in the variables that were being manipulated. The creative team in Odisha developed the scripts in Odia, the language the videos were filmed and produced in. English translations were used for discussions and feedback with the larger group, which consisted of health communication experts and a former Hollywood scriptwriter with expertise in storytelling. This approach to develop in Odia first, instead of transforming an English script to the language, improved the likelihood that the videos would be culturally relevant.

### Pilot-testing and finalization of the script

The manipulations were scripted into the dialogue across the eight videos in a way to ensure that the videos remained as close in length as possible to one another. Total time for each dialogue block and total number and lengths of different dialogue blocks were kept similar to ensure that there was minimal variance in length of videos.

Before the finalization of the script, the local team in India assembled a community advisory board of 11 individuals, representing diverse perspectives in the Odisha region. The majority of the advisory board members were young adults (under 35) and worked both inside and outside of healthcare. This included two young married couples with children, a doctor, a school principal, an accredited social health activist worker, and a journalist, among others. The group was evenly split between male and female participants. Board members were invited to provide feedback on video scripts. Audio-only versions were recorded for pretesting purposes only. Using a female narrator, four scripts were recorded: two humorous and two neutral, each featuring one individualistic and one collectivistic viewpoint. Board members were interviewed in one-on-one (or pairs for married couples) sessions over Zoom for a total of 10 interviews. Participants were able to re-listen to recordings upon request. Feedback was generally quite positive, with only minor edits suggested. Participants described the scripts as well-done overall, and generally helpful information for individuals who remain unvaccinated. The humorous videos were well received. Participants noted that the humor was used delicately, with a light touch, an important consideration given the seriousness of the subject matter and how many in the community had experienced loss related to COVID-19. Participants could also confidently detect the differences between the individualistic and collectivistic focuses – but did not say which they felt was more effective. The scripts were edited to reflect this feedback before being sent to the filming team.

### Video pre-production

**
*Camera & production crew*
**

A professional production team was engaged, consisting of a national-award winning filmmaker, an assistant director, a director of photography, and other crew members. Production logistics were designed to ensure that all the shots would look similar, which meant that the set décor, props, clothing and look etc. would be similar across the multiple days of shooting. A Black Magic Ursa MiniPro 4.6k camera with CP3 lenses was used to film the videos. The Final Cut Pro X was used for editing and the Davinci Resolve 17 was used for color grading on a MacOS.

**
*Casting*
**

For the role of the protagonist, versatile actors able to act in non-humorous as well as humorous roles were selected through auditions. Other actors were recruited based on earlier roles they had portrayed in various media productions. The cast members also understood the scientific aspects of the project, such as the need for reducing improvising in acting and to remain aligned with the script.

**
*Location selection*
**

Various locations were scouted, before deciding on the final location, which was a house in a village near Puri, Odisha, which reflected a rural/ semi-urban setting. The location fit well in the story and was also visually appealing.

### Video production approach

 Scholarly programs have isolated and identified different ways that film and video formal features can affect viewing audiences. Formal features in film and video are defined as specific production techniques that are independent of content, message, or story. These features include cuts, dissolves, fades, zooms, angles, sound effects, and more. We sought to keep formal features constant across the different videos, based on findings about how they can have significant effects on viewer experiences
^
70–
73
^. The entire filming for the eight videos was divided into shots, and similar shots from across all videos were filmed together to ensure that all of them had the same camera angle, focal lengths, pans, zooms, and backdrop weather conditions to align across all eight scripts.

### Post-production editing

 The editing process began with the selection and cataloging of shots as per the various scripts. The first video was created with all the shots and their sequences in the video being documented. The remaining videos were created by using the first video as a template and changing the specific shots as necessary. Put another way, we did not shoot each video from beginning to end before shooting the subsequent video. Rather, we kept the camera focused in a particular way and then shot all eight scenes pertaining to that camera angle before moving on to the next scene. A sample of the shot list for the template video is shown in
Table 1 which was used as a guide to ensure consistency across the eight videos. Each video was subsequently reviewed by a member of the creative team well versed with the research needs and aims, to ensure similarity as well as accuracy in the variations. This post-production editing can be a complex process due to a high volume of seemingly similar but different shots, especially if the creative team members are not familiar with this approach of making videos.

**Table 1. T1:** Description of shot list sample from the template video.

Video	Start	Stop	Camera	Scene
**Template**	0.00	0.03	Close up	Cake being cut
	0.04	0.07	Close up	Helmet on Table
	0.08	0.11	Wide	Munna (the male protagonist) being greeted
	0.12	0.15	Two shots	Handing cake

### Dissemination

 After conducting the online experiment, we selected two of the eight videos for dissemination so that we could also study the comments they would generate from viewers and conduct a social network analysis of the viewers themselves. We chose only two videos (and not all eight) so as to minimize perceptions of repetition by the audience. We selected the female, individualistic, non-humor video and then the diametrically opposite one that differed on all three variables (hence a male, collectivistic, humor video). Dissemination was done on the Swasthya Plus Network (SPN) Odia website, Facebook page, and YouTube channel
^
74
^. The videos were given titles, descriptions, and thumbnails to generate curiosity and interest. A conscious effort was made to ensure the videos did not resemble vaccine public service announcements, given the perceived fatigue among the audience toward such messaging. The videos were disseminated across both platforms, with an intentional posting gap between the release of the first and second video. The video links were then shared with tens of thousands of people connected with Swasthya Plus and partners via WhatsApp.

### Evaluation of videos

Videos will be evaluated in 3 ways:

1. Online experiment,2. Qualitative investigation via focus groups/ interviews,3. Social media analysis.

**
*Online experiment*
**

The online experiment was a survey questionnaire hosted on the
Qualtrics platform with four parts: consent, pre-exposure questions, video randomization, and post-exposure questions. The survey questionnaire was developed specifically for this project, but included scales on general vaccine hesitancy and individualism/collectivism adapted from previously published work by Quinn
*et al*. 2019 and Singelis
*et al*. 1995, respectively
^
10,
42
^. Additional questions were added based on the specific context of COVID-19, the target audience of young adults, and the setting of Odisha, India. The final questionnaire was not validated, however all the team members (N=13) pilot tested the questionnaire, and the final version was created taking into account the local setting in Odisha, comments and discussions from the team and being mindful of how long it would take respondents to complete it. The questionnaire can be found as
*Extended data*
^
75
^.

The survey was expected to take each participant 20–30 minutes to complete and participants were compensated on completion. To recruit participants for the online experiment component, our partner Swasthya Plus Network advertised the experiment through a link on their WhatsApp channels. 2,349 responses were collected over a six-day period in February 2022.

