## Measurement

### Statistical analysis and power calculation

**Online experiment component:** We assumed that, prior to exposure, 30% of the population would be vaccine-hesitant and that exposure would affect the attitudes of 10% of the viewers. To achieve power of 80%, with an alpha of 5%, the required sample size would be 294 per group, which we rounded up to 300. To be able to conduct sub-analyses along caste (three subgroups) and three age groups (i.e., nine groups in total), the overall required sample size was calculated to be 2,700. 

**Data analysis**. Data analysis will be done in two phases. First, we will conduct manipulation checks for the three variables that were manipulated. We manipulated the scripts to have either an individualistic or a collectivistic appeal. Responses to questions that asked about the extent to which the videos had an individualistic appeal (coded as 1) or a collectivistic appeal (coded as 5) will be subjected to a t-test in which the assignment to condition (individualistic or collectivistic) will be the independent variable. Similarly, the extent to which the videos were perceived to be humorous will also undergo a t-test. Finally, we will ask participants to recall whether the main protagonist was a male or female. This will be compared against the assignment variable (whether assigned to the male or female protagonist) through a chi-square test. If the results of the two t-tests and the chi-square test are significant, we will deem the manipulations to have been successful. Second, we will run an analysis of covariance (ANCOVA) model in which assignment to experimental conditions will be the three independent variables (individualistic or collectivistic appeal; humor or serious tone; and protagonist gender) and attitudes toward vaccines will be the dependent variable. In this model we will control for demographic indicators. We will also test for three two-way and one three-way interactions among the independent variables.

**Qualitative component:** From the survey respondents (
*n*=2,700), we will identify the 10% (

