*n*=270) with greatest vaccine hesitancy, as determined through their pre-exposure scores on the vaccine confidence index. This subsample will be invited to participate in focus groups. From this pool, we will purposively select participants to fill up to 12 focus groups, each with 8 participants. To ensure we hear diverse viewpoints from different segments of the population, groups will be stratified by both age (18–22, 23–30, 31–45) and gender (male, female). Following this design, we expect a maximum of 100 participants (
Table 2).

**Table 2. T2:** Expected numbers and description of focus group (FG) participants.

	Male	Female	Total
Age 1: 18–22 years	2 FGs ( *n*=16)	2 FGs ( *n*=16)	4 FGs ( *n*=32)
Age 2: 23–30 years	2 FGs ( *n*=16)	2 FGs ( *n*=16)	4 FGs ( *n*=32)
Age 3: 31–45 years	2 FGs ( *n*=16)	2 FGs ( *n*=16)	4 FGs ( *n*=32)
Total	6 FGs ( *n* =48)	6 FGs ( *n* =48)	12 FGs ( *n*= 96)

Additionally, time and resources have been allocated to conduct semi-structured online interviews with up to 20 additional people to delve deeper on any emergent topics that may arise over the course of the study. This would lead to a maximum of 120 participants in the qualitative portion of the study.

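### The planning target of 2,700 is reported as the number randomised and surveyed, while only 2,349 responses are reported, and the gap, the experiment's status and its dates are not reconciled

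*Protocol article*

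**What the plan says.** All references are to the protocol article.

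- **Study design** reports, in the past tense, that "Odia-speaking participants (N = 2,700) between the ages of 18–35 years were randomly assigned to watch one of the eight study videos". It places the launch of the experiment in January 2022.
- **Evaluation of videos, Online experiment** reports that "2,349 responses were collected over a six-day period in February 2022".
- **Statistical analysis and power calculation** derives 2,700 as a requirement. It assumes that "prior to exposure, 30% of the population would be vaccine-hesitant" and that "exposure would affect the attitudes of 10% of the viewers", with 80% power and alpha 5%. This gives 294 per group, rounded to 300, multiplied by nine caste-by-age subgroups.
- **Qualitative component** of the same section treats 2,700 as the number of survey respondents. It takes 10% of them (270), those "with greatest vaccine hesitancy, as determined through their pre-exposure scores on the vaccine confidence index", as the pool to invite to focus groups, with at most 120 qualitative participants overall.
- **Dissemination** says: "After conducting the online experiment, we selected two of the eight videos for dissemination".
- **Study status** says that the videos have been disseminated, but describes the online experiment only as having begun.

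**The concern.** How many people were randomised is the first figure needed to read any trial, and the article gives two counts that do not agree. The higher one equals the planning target exactly, which suggests that the target was carried over as if it had been achieved. Left as it is, the wrong denominator could pass into later reports and into any account of losses after randomisation.

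The nine-subgroup argument is the article's only justification for 2,700. If 2,349 is what was obtained, that justification is no longer met. A reader also cannot tell whether 2,349 is a final count or an interim one, because the statements on status and dates do not line up.

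**Working it through.** **1. Reproduce the planning figure.** Inputs from the power section: 30% hesitant before exposure and a 10% change, 80% power, alpha 5%. I read the change as 10 percentage points (30% v 20%) and alpha as two-sided, because these readings return the article's 294. With pooled variance under the null and no continuity correction:

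n = [1.960·√(2·0.25·0.75) + 0.842·√(0.30·0.70 + 0.20·0.80)]² / 0.10² = [1.200 + 0.512]² / 0.01 ≈ 293.2, rounded up to **294**.

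Rounded to 300, 9 × 300 = **2,700**. The target is correctly derived from its inputs.

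**2. Compare the counts.** 2,700 − 2,349 = **351**, and 351 / 2,700 = **13.0%**.

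**3. Put 2,349 in place of 2,700**, on the same two-proportion basis, with power = Φ[(0.10·√n − 1.200) / 0.608]:

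| Unit | n at 2,700 | Power | n at 2,349 | Power |
|---|---|---|---|---|
| Caste-by-age subgroup (÷ 9) | 300 | 80.9% | 261 | 75.3% |
| One video (÷ 8) | 337.5 | 85.2% | 293.6 | 80.1% |
| One level of a factor (÷ 2) | 1,350 | >99.9% | 1,174.5 | >99.9% |

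Worked example for 261: (0.10·16.155 − 1.200) / 0.608 ≈ 0.683, and Φ(0.683) ≈ 0.753.

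Nine subgroups of 294 need 9 × 294 = 2,646 people. Since 2,349 is below 2,646, they cannot all reach 294, however the sample divides. The 75.3% does need equal subgroups, which the article does not state.

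**4. Focus-group pool.** 10% of 2,349 = 234.9, about **235** instead of 270. Against at most 120 places, 235 / 120 ≈ 2.0.

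**5. Status and dates side by side.** Study design gives a January 2022 launch. The Online experiment section reports six days of collection in February 2022 and no January responses. Dissemination places the choice of the two videos after the experiment. Study status says that dissemination has happened, yet that the experiment has begun. The second and third statements point to a closed experiment; the last does not.

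**The case against.** The strongest defence is that 2,349 is undefined. Responses could mean all submissions, eligible randomised participants or completers. If 2,700 were randomised and 2,349 completed (87%), the Study design sentence would be true and the gap would be attrition. This stands as far as the remedy goes: overwriting 2,700 with 2,349 could introduce an error. It does not remove the contradiction. The article never says this, the qualitative plan calls the 2,700 survey respondents, and on this reading a 13% loss after randomisation goes unreported.

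A second defence is that little depends on the gap. This is largely right for the main question: main effects and comparisons of two videos keep their power, and 235 invitees cover the qualitative places.

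Four stronger readings are tempting, and the documents do not support them:

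- *That the power calculation is wrong.* It reproduces, and it is stated as a requirement. A missed target does not falsify it.
- *That the experiment is certainly closed.* The Dissemination and Online experiment sections suggest so, but Study status does not agree.
- *That 75% is the power for comparing videos within a subgroup.* Each subgroup is spread over all eight videos. A main-effect comparison inside an average subgroup has about 130 per side (261 / 2) and about 46% power, or 150 per side and about 52% even at 2,700.
- *That late recruits would already have seen the released videos.* No section proposes recruiting after dissemination, so this harm is hypothetical.

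**Conclusion.** The concern holds as an unreconciled contradiction. A planning target appears as the number randomised and as the number of survey respondents, while the only reported collection count is 351 (13.0%) lower. The experiment's status and dates are also inconsistent.

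The statistical consequence is limited. If 2,349 is the achieved number, the article's own condition for its caste-by-age sub-analyses is not met (average 261 against 294, about 75% power instead of 80% on the article's basis). Power for the main analysis is hardly touched. The conclusion rests on three assumptions: that 2,349 is the number available for analysis, that the change is 30% to 20% tested two-sided, and, for the power figures, that subgroups and arms are of equal size. The contradiction between the counts needs none of them.

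**What to change.** 1. In the power section, keep 2,700 and label it as the target only.
2. In Study design, replace the statement that 2,700 were randomised with the actual number. Report 2,349 as the responses collected, define responses, and give the numbers randomised, completed and analysable separately.
3. In the Qualitative component, correct the respondent count and the pool (about 235 if 2,349 is the respondent count).
4. If 2,349 is the achieved number, say that the 294 to 300 per subgroup behind the 80% power was not reached on average. Do not present 75% as the power of comparisons between videos within a subgroup.
5. Reconcile the experiment's status and dates across Study design, Dissemination, Online experiment and Study status.

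The cost is text only. Randomisation, the main analysis and the qualitative design do not change. The stated basis for the subgroup analyses becomes somewhat less favourable.
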